##### Recruitment period

Participants enter a two-week period where they may recruit and educate a small number of peers and provide them with recruitment coupons. Those peers then contact the study directly to be screened, and the participant continues in the study. Participants may decline to recruit peers and continue in the study.

##### Intervention session #2

Participants return for a second one-on-one intervention session two weeks after their initial session. During this session, CDC required pre-test counseling is provided to assess readiness and desire for testing. If participants decide to test, standard consent is obtained, followed by the OraQuick Advance Rapid HIV-1/2 Antibody Test with oral mucosal fluid. While the test is processing, subjects complete a computerized HIV prevention and risk-reduction program, called CARE for Prevention [56]. If the rapid HIV test is non-reactive, participants are counseled and provided referrals, and their involvement in the study is complete.

For reactive tests, a second OraQuick Advance Rapid HIV test is administered, similar to local health department protocols, to minimize false positive results on site [57]. An OraSure Western Blot confirmatory test is also conducted, with results available in 1-2 weeks. Participants are then asked to provide blood specimens for HIV viral load and CD4 testing. Because some newly diagnosed participants decline to provide blood at diagnosis, they may do so at a future contact if they so choose. Navigation (described below) may begin at this point for intervention arm participants who have serious barriers to engaging in future study activities, including meeting to receive confirmatory results, or the session may end after the blood specimen is provided and navigation may begin at Session 3.

##### Intervention session #3

Newly diagnosed participants are provided confirmatory test results and post-test counseling following CDC and local guidelines. Those in the control arm receive standard post-test counseling with referral to HIV health care and up to three phone reminders to attend the appointment. For intervention-arm participants, the session then turns to a discussion of the navigation component of the BCAP PDI. Participants receive compensation for each session ($30) and blood draws ($25), plus local round-trip public transportation.

#### Treat and retain phase activities

##### Navigation

Navigation is a flexible and individualized intervention approach to reduce disparities in care for low income or marginalized populations [58, 59]. In practice, navigation identifies and resolves the organizational, social, and individual barriers patients may experience to accessing these services [60]. In the BCAP PDI, navigation uses a strengths-based approach that draws on Motivational Interviewing techniques, guided by an Action Plan that is revisited over time. The aim of the Action Plan is to identify and resolve barriers to linkage to HIV care and support engagement in care. If there are no major barriers to care, the navigator can monitor and support engagement in care. If there are barriers (e.g., mental illness or substance abuse), navigation involves several options: communication with the primary care provider; screening and “fast track” referrals for substance use, mental illness, housing and other services; accompaniment to health care appointments; phone call reminders; and in-person meetings to support adaptation to the HIV diagnosis and linkage to care. Contacts are documented, and participants receive modest financial incentives for the first four navigation meetings to establish the working alliance during this critical period ($10 each).

#### Aspects of the PDI and assessments

##### Differences between the BCAP PDI and control arm

Intervention arm participants 1) receive peer education at the time of recruitment, which introduces them to the core messages, while controls do not receive peer education; 2) are trained to educate their own peers on the core messages that reinforce the core messages, while controls are trained only to recruit peers; and 3) the newly diagnosed receive patient navigation while controls receive treatment as usual (an HIV care appointment and follow-up phone calls), as shown in Fig. 1.

##### Network-based case finding

To increase access to the undiagnosed, participants who are newly diagnosed with HIV during the study are given the opportunity to recruit three additional peers, and encouraged to recruit sexual or injection drug-sharing partners if they choose. This is a form of network-based case finding [61, 62]. The newly diagnosed participant’s recruiter also receives coupons, as does one participant randomly selected from the same arm. This latter strategy is designed to protect the newly diagnosed participant’s confidentiality, as well as that of his/her recruiter, by masking the reason for receiving additional coupons.

##### Follow-up assessments

Participants in both arms are assessed at four time points: at Session 3, the time of diagnosis (the Time 2 [T2] assessment), and 3- (T3), 6- (T4), and 12-months post-baseline (T5). The T2, T3, and T4 interviews assess the prior quarter, and the T5 interview (12-month follow-up) assesses the prior 6 month period. The assessment includes measures on care engagement, satisfaction, understanding of HIV, and HIV medications prescribed, side effects, and adherence [63–65]. All assessments are conducted using ACASI and take approximately an hour. At T5, blood is drawn to measure CD4 count and HIV viral load; a Medical Report Form containing data on attendance at care appointments over the past year drawn from the medical record is also completed. Participants receive modest compensation for assessment activities ($25-$30).

#### Activities for those with previously diagnosed HIV infection at screening (“known positives”)

Participants with previous HIV diagnoses are hypothesized to be an important means of finding the undiagnosed [66]. Yet they also may be poorly engaged in HIV care, thereby in need of intervention. As noted in the section on Eligibility Criteria, the PDI/RDS study enrolls peers (but not initial seeds) with previously diagnosed HIV infection. At screening, the peer’s HIV status is confirmed with medical documentation. A baseline interview assesses the domains noted above, supplemented with data on HIV health status, engagement in care, experience with providers, and ART prescription and adherence [67]. Participants then engage in a single intervention session and are trained to recruit/educate (intervention arm) or recruit (control arm) peers, and their past-year HIV health care attendance patterns and satisfaction with care are evaluated to determine whether navigation to HIV care is required. Participants then have the opportunity to recruit 3-5 peers over a two-week period, and navigation to care is provided. At four months post baseline, a Medical Report Form capturing CD4, HIV viral load, and health care attendance over the past year from the medical record is completed.

#### Changes to procedures during implementation

Complex research studies often undergo refinements in their early stages. A number of changes were made to the initial study protocol over the first six months of implementation in response to high rates of ineligibility (> 40 %), insufficient rates of enrollment which stopped recruitment chains, low numbers of female participants, an imbalance between intervention and control arms, and low rates of HIV-infected participants in the study’s early phase of implementation. These study inefficiencies were reviewed by the study Principal and Co-Investigators, who made recommendations for adjustments. In response, changes to some eligibility criteria were instituted. Initially, participants were eligible if they had not been tested for HIV in the past year; were HIV negative or unknown status; were aged 18-*50* years; and resided only in the core seven zip code HRA. Further, there was initially no steering incentive for women. Third, the control intervention Session 1 was very brief (~5-10 min to orient participants and train them how to recruit peers, which was not sufficient for engagement). The changes to eligibility criteria reflected in the section above were designed to reduce ineligibility and improve study efficiency; steering incentives to boost the proportion of women in the sample; and increasing the duration of the control Session 1 is intended to improve engagement among the control arm participants. The final protocol described above will be implemented for > 75 % of the sample.

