#### Eligibility criteria and screening for eligibility

Study eligibility criteria are the same for initial seeds and peers with two exceptions. Study eligibility criteria are: age 18-60 years; sexually active (vaginal and/or anal sex) with at least one opposite sex partner within the previous year; reside in the larger HRA (but initial seeds must reside only in the core HRA); African American/Black or Latino/Hispanic race/ethnicity; comprehension of English or Spanish; unknown HIV status (for initial seeds only; peers may report previous HIV diagnosis); not actively psychotic; not a participant in the past local NHBS studies with HHR.

Peers present to the study with a coded recruitment coupon linking the recruiter to the recruit. Consenting recruits participate in a brief computerized screening interview to determine eligibility, including questions about their relationship with the recruiter. All screened participants are provided an incentive ($15) and *recruiters* are also compensated for each peer who presents to the study depending on peer eligibility ($5-25). Initial seeds are directly recruited by staff, as noted above, and are screened for eligibility using these same procedures. The next section describes procedures for participants who are HIV negative or do not know their HIV status at the time of screening, the main focus of the study, followed by a brief description of activities for those who enter the study with known HIV infection.

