#### Data analysis

The hypothesis for the main Treat and Retain aim is that compared with participants in the control arm, PDI arm participants will be more likely to 1) attend an HIV clinic appointment sooner; 2) initiate ART earlier; 3) achieve viral load suppression; and 4) be retained in HIV care during the 12-month follow-up period. Logistic regression will be used to compare groups on viral load suppression. Since HIV viral load assay results range from <50 to >100,000 copies/ml, other generalized linear models will examine intervention impact on median viral load, log transformed viral load, and on viral load dichotomized at 1,000 or 10,000 copies/ml, which have been associated with greater HIV transmission risk [68–71]. Cox proportional hazards regression will compare groups on time to first HIV clinic appointment and initiation of ART if indicated. Frailty models [72, 73] will examine intervention effects on first HIV clinic appointment and initiation of ART with participants clustered by recruitment chain. Covariates for these analyses will include prior HIV testing and initial viral load.

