### Eligibility criteria

The VBS eligibility criteria are the same as in the PDI/RDS study described above, with the following exceptions: VBS participants must reside in the core HRA (not the larger HRA), and those with previously diagnosed HIV are ineligible. Thus, the VBS eligibility criteria are: aged 18-60 years; sexually active (vaginal and/or anal sex) with at least one opposite sex partner within the previous year; reside in the core HRA’s seven zip codes; African American/Black or Latino/Hispanic race/ethnicity; comprehend English or Spanish; unknown or negative HIV status; not actively psychotic based on valid screening instrument.

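### Fewer than a quarter of participants entered under earlier eligibility rules and, for controls, a much shorter Session 1; the named analyses do not account for protocol phase, and the probable bias is modest

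*Protocol article*

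**What the plan says.** Under Changes to procedures during implementation (Part 1), the article lists early problems that led to changes over the first six months. Among them is "an imbalance between intervention and control arms", with no variable, size or direction given; low early rates of HIV-infected participants are another.

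What changed:
- **Testing history and HIV status.** "Initially, participants were eligible if they had not been tested for HIV in the past year; were HIV negative or unknown status". The current criteria have no past-year rule, and on status they read "unknown HIV status (for initial seeds only; peers may report previous HIV diagnosis".
- **Residence and age.** Early participants "resided only in the core seven zip code HRA" and were aged 18-50. Peers may now live in the larger HRA, and the upper age limit is 60.
- **Women.** A steering incentive was added.
- **Control Session 1.** It was about 5-10 minutes and judged too short to engage participants. Introductory intervention session #1 now gives 20-60 minutes.

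On how many are affected: "The final protocol described above will be implemented for > 75 % of the sample".

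On analysis, the Data analysis section (Part 1) says: "Covariates for these analyses will include prior HIV testing and initial viral load". The Analysis plan (Part 2) adjusts for demographic differences and prior HIV testing. Neither names protocol phase. The targets of 3000 RDS participants and about 254 analysable new diagnoses are given without separating early from late entrants.

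The Aims section describes the control as matched to the intervention for time and attention, with no exception for the early period. For venue recruits, the Eligibility criteria section in Part 2 says: "The VBS eligibility criteria are the same as in the PDI/RDS study described above", except that they must live in the core HRA and have no previous HIV diagnosis.

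**The concern.** Seeds are randomised 1:1, but each recruit takes the recruiter's arm, so the number of recruits per arm at any time depends on how well each arm's chains grow. The article reports an early arm imbalance and lengthened the control session to improve engagement of controls. If that shifted the arm ratio among recruits while eligibility was also changing, protocol phase would be related both to arm and to the kind of participant enrolled. A pooled comparison without phase could then attribute part of an early-versus-late difference to the intervention.

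A second issue is separate from confounding. The early control condition was not the later one, so the early contrast between arms differs from the late one. No baseline covariate corrects that.

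In Seek and Test, early and late RDS recruits differ from VBS recruits in different ways, so the RDS-VBS contrast mixes sampling method with eligibility.

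**Working it through.** **1. The plan's own figures.** New diagnoses analysed: 3000 x 0.10 x 0.85 = 255 (stated 254). Design effect with 80 chains and ICC 0.20: 1 + (254/80 - 1) x 0.20 = 1.435; 254/1.435 = 177 (stated 176). At 80% power and two-sided alpha 0.05, with 30% control suppression, the detectable OR is 2.07 for n = 254 and 2.39 for n = 176. These reproduce and are not in dispute; they serve as a yardstick.

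**2. Size of the early phase.** At most 0.25 x 3000 = 750 participants and, if new diagnoses were spread evenly, 0.25 x 254 = about 64 cases. The reported low early HIV rates point to fewer.

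**3. Bias in Treat and Retain when the true OR is 1.** In each arm, suppression = e x p_early + (1 - e) x p_late, where e is the arm's early share. The article gives neither e nor phase-specific rates, so all are assumed.

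With p_early = 20% and p_late = 35%:
- e = 35% PDI, 15% control: 0.2975 v 0.3275, OR 0.87.
- e = 35% PDI, 10% control: 0.2975 v 0.3350, OR 0.84.
- e = 17% PDI, 7% control (about 12% early overall): 0.3245 v 0.3395, OR 0.93.

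With an overall early share f, a fraction a of early cases in PDI, and late cases split equally, e is f x a / (f x a + (1 - f)/2) in PDI; for control, replace a by 1 - a. Pooled null ORs:

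| f | early split, PDI:control | 15% early, 30% late | 15% early, 45% late |
|---|---|---|---|
| 10% | 60:40 | 0.97 | 0.96 |
| 25% | 60:40 | 0.94 | 0.91 |
| 25% | 2:1 | 0.91 | 0.85 |
| 25% | 3:1 | 0.86 | 0.78 |
| any | 50:50 | 1.00 | 1.00 |

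If the early excess was in the control arm, each value inverts. At f = 25%, ignoring clustering, type I error is 5.5-6.6% for a 60:40 split and 6.4-9.5% for 2:1. The 3:1 row (8.1-15.4%) combines the largest possible early share with a severe imbalance and is an extreme.

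**4. Cost of a phase term.** The variance of the arm effect rises by 1/(1 - r²), where r is the arm-phase correlation. For f = 25% and splits of 60:40, 2:1 and 3:1 this is 1.01, 1.02 and 1.05.

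**5. Arm-by-phase interaction.** With 25% of 254 cases early and an OR of 2.07, the ratio of ORs detectable at 80% power is about 5.2-7.9 for control suppression of 15-45%, before clustering. It cannot serve as a test.

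**6. Seek and Test.** Assume 12% undiagnosed prevalence in those untested in the past year, 4-6% in others, and one-half to two-thirds of VBS recruits untested in the past year. With 25% of RDS recruits early, RDS = 0.25 x 12% + 0.75 x VBS:
- half untested, 4%: VBS 8.0%, RDS 9.0%, OR 1.14;
- half untested, 6%: 9.0% v 9.75%, OR 1.09;
- two-thirds untested, 4%: 9.3% v 10.0%, OR 1.08;
- two-thirds untested, 6%: 10.0% v 10.5%, OR 1.06.

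This is before any adjustment. It works only through recent testing, which adjustment for prior testing would largely remove if coded by recency.

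**7. Cost of restricting the RDS side.** Taking variance as proportional to 1/n_RDS + 1/400, going from 3000 to 1500 records (an assumed loss of half) gives 0.003167/0.002833 = 1.12. With ICC 0.20 and all 80 chains still represented, the effective n goes from 361 to 1500/4.55 = 330, and the ratio is (1/330 + 1/400)/(1/361 + 1/400) = 1.05.

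**The case against.** The strongest reply is that this is an omission from a condensed article. The covariate lists say what models will include, not that nothing else enters; the full analysis plan may contain a phase term; and the changes are openly disclosed. That stands in part. The point still merits raising because this document itself reports the mid-trial change and the arm imbalance, then names an adjustment set that does not reflect them. Pooling is inferred from the single targets and single analyses; it is not stated outright.

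Three stronger readings are tempting, and the document does not support them.

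- **A reader might infer that the reported imbalance shows confounding by phase.** It does not. No variable, size or direction is given, and an arm imbalance that persisted unchanged would leave the early-to-late mix equal and cause no bias. Permuted blocks also keep seed allocation balanced over time.
- **A reader might infer that the past-year testing rule raised RDS yield over VBS.** Nothing supports a higher early yield. The article reports low early rates of HIV-infected participants, although excluding known positives may explain part of that. It does not say which rules VBS used at first. Early RDS entrants match the VBS residence and HIV-status criteria better than later ones, so dropping them would not by itself make the samples more alike. Planned adjustment for prior testing and demographics covers much of the rest.
- **A reader might infer that a quarter of the sample had a different comparator.** The short session affected only early controls. Session 1 concerns peer recruitment and staying in the study; control referral to care takes place at Session 3, which is not listed as changed.

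It is also fair that protocol phase at enrolment is a poor adjustment variable. Enrolment follows seed randomisation, depends on chain growth that the intervention may influence, and splits chains. The changes came over six months, perhaps in steps, so an undated initial/final split is not defined. The fix takes this into account.

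**Conclusion.** The concern holds in limited form. Fewer than 25% of the RDS sample entered before the final protocol, under different eligibility rules and, among controls, a much shorter Session 1. An early arm imbalance is reported and no phase term is named. The Aims description of the control and the account of its early Session 1 do not agree and must be reconciled.

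For Treat and Retain the bias is probably modest: null ORs of about 0.84-0.97, or 1.03-1.19 if reversed, against detectable ORs of 2.07-2.39. Only the extreme 3:1 case with 15% v 45% suppression goes further, to 0.78. All of this rests on assumed early shares, arm splits and suppression rates, and there is no bias if the early-to-late mix is equal by arm. The low early HIV rates argue for the mild end.

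For Seek and Test, 1.06-1.14 is an unadjusted illustration under assumed prevalences. Its direction is not supported by the document. The firmer problem there is that the RDS and VBS samples are not held to common criteria.

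**What to change.** **Treat and Retain**
- Fix the dates of the changes and define phase in advance by the seed's randomisation date, which keeps chains whole; use enrolment date as a sensitivity definition.
- Include phase as a covariate in the outcome models.
- Report the arm effect restricted to final-protocol participants as a sensitivity analysis. The covariate handles confounding by phase; only the restriction addresses the changed control session.
- Present any arm-by-phase contrast as descriptive only.
- Tabulate enrolment and new diagnoses by arm and phase, so that the imbalance can be judged.
- Reconcile the Aims wording on the control with the account of its early Session 1.

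**Seek and Test**
- Limit the RDS side to enrolees who meet the VBS criteria (core-HRA residence, no previous HIV diagnosis), whatever their phase.
- Code prior testing by recency so that it captures the early past-year rule.
- Report results with and without early-phase RDS recruits.

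**Cost.** One extra covariate, a rise of about 1-5% in the variance of the arm effect, and fewer RDS records. Even losing half of those would raise the variance of the RDS-VBS contrast by only about 12% without clustering, because the 400 VBS participants are the main limit. With ICC 0.20 the rise is about 5%, because the number of chains then matters more than the number of records. No change to recruitment or target sizes is needed.

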#### Data analysis

The hypothesis for the main Treat and Retain aim is that compared with participants in the control arm, PDI arm participants will be more likely to 1) attend an HIV clinic appointment sooner; 2) initiate ART earlier; 3) achieve viral load suppression; and 4) be retained in HIV care during the 12-month follow-up period. Logistic regression will be used to compare groups on viral load suppression. Since HIV viral load assay results range from <50 to >100,000 copies/ml, other generalized linear models will examine intervention impact on median viral load, log transformed viral load, and on viral load dichotomized at 1,000 or 10,000 copies/ml, which have been associated with greater HIV transmission risk [68–71]. Cox proportional hazards regression will compare groups on time to first HIV clinic appointment and initiation of ART if indicated. Frailty models [72, 73] will examine intervention effects on first HIV clinic appointment and initiation of ART with participants clustered by recruitment chain. Covariates for these analyses will include prior HIV testing and initial viral load.

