#### Study design using PDI/RDS

As noted above, RDS begins with direct recruitment of a small number of initial seeds who start recruitment chains by recruiting their peers into the research [36, 38]. In the present study, initial seeds are randomized to an intervention or control arm at a 1:1 ratio. Further, eligible and consenting peers who are subsequently recruited into the study are assigned to the same arm as their recruiter. Thus each initial seed and the peers subsequently enrolled in his/her recruitment chain are considered a cluster. This cluster randomized controlled trial design is necessary because intervention activities begin at the time of recruitment, when recruiters educate peer recruits on core messages. Because the statistical power of a clustered trial increases with the number of clusters, we plan to recruit more seeds than is typical in RDS (namely 40 seeds per arm), with a target sample size of 3000 individuals. The PDI/RDS study component also includes those with previously diagnosed infection (called “known positives”), and will describe HIV health indicators and engagement in HIV care among this subgroup. Study activities are approved by the Institutional Review Board at the NYU School of Medicine, and the protocol is registered with clinicaltrials.gov (NCT01607541).

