#### Power analysis

We estimate 10 % of all participants will be newly diagnosed with HIV infection and assume an attrition rate of 15 % at the last follow-up among those with newly diagnosed HIV infection (*N* = 254). We estimate the smallest detectable difference in proportion between PDI and control arms given a desired power of 80 % and α = .05. Assuming 15-45% of control participants achieve HIV viral load suppression within 12 months, odds ratio of 2.07 are detectable. With an ICC as high as .20 due to clustering by 80 seeds, the effective sample size is *n* = 176 and odds ratios of 2.39 are detectable.

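### Viral load suppression, the only powered Treat and Retain outcome, is assigned a logistic model with no cluster term, although recruitment chains are the randomised clusters

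*Protocol article*

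**What the plan says.** The section Study design using PDI/RDS sets up a cluster trial: "initial seeds are randomized to an intervention or control arm at a 1:1 ratio", peers inherit their recruiter's arm, and "Thus each initial seed and the peers subsequently enrolled in his/her recruitment chain are considered a cluster".

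The Part 1 Power analysis is for viral load suppression and carries that design through. It begins with N = 254 and a detectable odds ratio of 2.07. Then, "With an ICC as high as .20 due to clustering by 80 seeds", it reduces the effective sample size to 176 and raises the detectable odds ratio to 2.39. No other Treat and Retain outcome has a power calculation.

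The Part 1 Data analysis section states: "Logistic regression will be used to compare groups on viral load suppression". Median, log-transformed and dichotomised viral load go to other generalized linear models. None of these is given a random effect, GEE structure or robust variance. The covariates listed are prior HIV testing and initial viral load. For the time-to-event outcomes the same paragraph says "Cox proportional hazards regression will compare groups on time to first HIV clinic appointment and initiation of ART if indicated", and then "Frailty models [72, 73] will examine intervention effects on first HIV clinic appointment and initiation of ART with participants clustered by recruitment chain".

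**The concern.** An individual-level logistic model treats the 254 participants as independent. If outcomes within a chain are correlated, that model understates the standard error of the arm effect, because arm varies only between chains. The p-value is then too small and the confidence interval too narrow, on the one outcome for which the trial's ability to detect an effect was calculated.

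The document also disagrees with itself. The power section pays for clustering on this outcome, and the analysis section does not name a model that uses what was paid for. The paragraph addresses clustering for two outcomes and leaves it out for the viral load measures.

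**Working it through.** **Inputs**
- 80 chains and 3000 participants: "namely 40 seeds per arm), with a target sample size of 3000 individuals" (Study design using PDI/RDS).
- Newly diagnosed share: "We estimate 10 % of all participants will be newly diagnosed with HIV infection" (Part 1 Power analysis). With 15% attrition, 3000 × .10 × .85 = 255; the protocol states 254.
- ICC up to .20, α = .05, power 80% (same section). Sidedness is not stated. Two-sided is assumed, and it reproduces the protocol's figures.

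**Step 1. Reproduce the protocol's figures.** Mean cases per chain: m = 254/80 = 3.175. Design effect: DE = 1 + (m − 1) × ICC = 1 + 2.175 × .20 = 1.435. Effective n = 254/1.435 = 177, against 176 stated. With a 30% control rate (midpoint of the stated 15–45%), 1:1 split and no continuity correction, the detectable odds ratios are 2.07 at n = 254 and 2.39 at n = 176, as stated.

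**Step 2. Actual error of the unclustered test, equal chains.** The independence model understates the variance by the factor DE, so the actual two-sided error is 2 × [1 − Φ(1.96/√DE)].

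| ICC | DE | Actual error (formula) | Simulated |
|---|---|---|---|
| .05 | 1.109 | 6.3% | 6.1% |
| .10 | 1.218 | 7.6% | 7.5% |
| .15 | 1.326 | 8.9% | not run |
| .20 | 1.435 | 10.2% | 10.0% |

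The simulation applied the Wald test of the log odds ratio under the null: beta-binomial outcomes, 80 chains, N = 254, 30% suppression, 20,000 runs per setting. At ICC 0 it gave 4.9%.

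**Step 3. Unequal chains.** With coefficient of variation CV of cases per chain, DE = 1 + [(1 + CV²) × m − 1] × ICC.

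- *Chance variation only.* Take equal chains of 3000/80 = 37.5 people, 10% diagnosed and 85% retained. The variance of diagnosed cases is 37.5 × .10 × .90 = 3.375. After attrition it is .85² × 3.375 + .85 × .15 × 3.75 = 2.917, around a mean of 3.1875, so CV = 0.54. At ICC .20, DE = 1.617 and the error is 12.3%. At ICC .10, DE = 1.309 and the error is 8.7%.
- *Bunched cases, CV = 1.5 (assumption).* At ICC .20, DE = 1 + (3.25 × 3.175 − 1) × .20 = 2.864 and the error is 24.7% (simulated 24.5%).
- *Is a CV near 1.5 conceivable?* The Part 2 Power analysis allows an ICC as high as .20 for undiagnosed infection. At that ceiling the variance of cases is 3.375 × (1 + 36.5 × .20) = 28.01, or 20.72 after attrition, so CV = 1.43. The error is then 23.6% at an outcome ICC of .20, 10.2% at .05 and 7.0% at .02.

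**Step 4. Cost of the correct analysis.** √1.435 = 1.198, so intervals are about 20% wider at ICC .20 with equal chains. At DE = 2.864, √2.864 = 1.69, about 69% wider.

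**The case against.** The strongest reply is that the article names a model family and does not say that clustering is ignored. Logistic regression can carry a random effect or a robust variance, the authors plainly know that the trial is clustered, and a fuller analysis plan may supply the term. It stands that the omission is read from the plain model name and from the contrast with the next sentences, and that a reader should not infer a decision to ignore the chains. It does not remove the point. The paragraph does specify clustering, for two outcomes only, so followed as written it gives the powered outcome a model that does not match the design or the power calculation.

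Three stronger readings are tempting and are not supported:
- *That the error is at least 10%.* That figure needs the ICC of .20, which the protocol gives as an upper value. At smaller ICCs with equal chains it is 6% to 9%. The 25% figure needs strong bunching of cases as well. The protocol's ICC for undiagnosed infection makes such bunching possible only at its own ceiling, so two upper values are being combined.
- *That the whole Treat and Retain comparison is affected.* The Aims list four outcomes, with time to a clinic appointment first. That outcome and ART initiation do have a chain-clustered model. Suppression is the only powered outcome; the document does not call it the primary one.
- *That naming both Cox and frailty models is an error.* The two sentences can be read as one approach, the second supplying the clustering. Which result decides is mostly a matter for the analysis plan.

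**Conclusion.** The concern holds. The viral load models as stated do not match the unit of randomisation, the protocol's own sample-size reasoning, or the treatment of the time-to-event outcomes. The direction is certain for any positive ICC; the size depends on the ICC and on how cases fall across chains. With equal chains the nominal 5% test runs at about 6% (ICC .05), 7.6% (.10) and 10% (.20). Equal chains are the most favourable case: chance variation alone gives about 12% at ICC .20, and a CV of about 1.5, which is an assumption, gives about 25%. The document offers some reason to expect uneven chains: it reports chains that stopped early (Changes to procedures during implementation), and it gives extra coupons around new diagnoses (Network-based case finding). It gives no figures from which to fix a CV.

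**What to change.** In the Part 1 Data analysis section, state that viral load suppression and the other viral load models are fitted with clustering on the initial seed. Use a mixed-effects or GEE model with small-sample-corrected standard errors, with degrees of freedom based on the number of seeds that contribute cases. Median viral load needs its own method, such as cluster-robust quantile regression or a bootstrap that resamples whole chains. Preferably, also state that the chain-frailty model is the deciding analysis for time to first appointment and time to ART.

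No new data are needed. The coded coupons link recruiter to recruit (Eligibility criteria and screening for eligibility), and tracking of chains is listed as an essential element of the sampling method, so each participant's seed can be derived by tracing the chain back.

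The cost is precision: intervals about 20% wider at ICC .20 with equal chains, and more if cases bunch. For equal chains, this is the loss already built into the stated effective n of 176 and detectable odds ratio of 2.39.
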